#### Primary

The primary analyses will compare the six-month change in primary outcomes (hospital days and number of rehospitalisations) between the PSW+ and PSW- groups. We will carry out both intention-to-treat and per-protocol DID analyses for the two primary outcomes, presenting adjusted and unadjusted results [62]. To be included in the per-protocol analysis, participants in the PSW+ arm must receive at least one recorded ward visit and three recorded community visits during the six-month follow-up period [62]. As described above, disability and family support are potential confounders and will be included as covariates in the adjusted analysis.

We will use multivariable linear regression unless the distribution is skewed, in which case we may consider a Poisson or negative binomial regression, or another appropriate method. The impact of the peer support programme on hospital days and rehospitalisations will be estimated through mixed effects models with a random effect to account for correlations among users with the same PSW and fixed effects for access to peer support (PSW+ group versus PSW-group), time (baseline versus follow-up) and the interaction between access to peer support and time. The interaction estimating the change from baseline to follow-up in the PSW+ group relative to change in the PSW- group is the key effect of interest. We will tabulate the results at follow-up and differences from baseline by group with corresponding 95% confidence intervals.

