**Methods:**

This protocol describes a quasi-experimental difference-in-differences study conducted as part of a broader evaluation of the Brain Gain II peer support programme based at Butabika National Referral Hospital in Kampala, Uganda. The primary objective is to investigate whether frequent users of psychiatric inpatient care who have access to a peer support worker (PSW+) experience a greater reduction in rehospitalisation rates and number of days spent in hospital compared to those who do not have access to a peer support worker (PSW-). Frequent users, defined as adults diagnosed with either a mental disorder or epilepsy who have had three or more inpatient stays at Butabika over the previous 24 months, are referred to Brain Gain II by hospital staff on five inpatient wards. Frequent users who normally reside in a district where peer support workers currently operate (Kampala, Jinja, Wakiso and Mukono) are eligible for formal peer support and enter the PSW+ group. Participants in the PSW+ group are expected to receive at least one inpatient visit by a trained peer support worker before hospital discharge and three to six additional visits after discharge. Frequent users from other districts enter the PSW- group and receive standard care. Participants’ admissions data are extracted from hospital records at point of referral and six months following referral.

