### Peer support

All participants receive standard adult care and may have some contact with PSWs via the Recovery College. Additionally, participants in the PSW+ group receive face-to-face visits from a trained PSW. Each participant in the PSW+ group is assigned a PSW from a nearby community by an administrator in the Peer Support Office. Peer support visits are offered for up to six months after a PSW is assigned to a user. A recipient of peer support will be visited by a PSW at least once on the ward before discharge, and at least three times after discharge. For particularly vulnerable cases (i.e. three or more inpatient stays in the past 12 months), up to six visits can be made. The PSW visits occur per the recipient’s preference, either at home, at a meeting point in the community, or at the hospital when the recipient returns for outpatient visits. The carer may also be engaged in peer support visits, where possible.

The peer support visits delivered by PSWs are flexible and unstructured, and may consist of any or all of the following:
**Befriending** (social contact, supportive listening and encouragement);**Role-modelling** (sharing personal experiences of illness and recovery);**Psychoeducation** (education on recovery principles);**Problem-solving** (discussing current challenges and possible solutions, liasing with providers to resolve issues with medical and social care as needed).

The qualifications, training, supervision and compensation of PSWs as well as quality assurance for peer support visits are detailed in Table 1.

**Table 1 Tab1:** Brain Gain II Peer Support Workers

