### Outcomes

For variables to be included in the primary analysis, Table 2 summarises the time-points for assessment, the form used and the data collector responsible.

**Table 2 Tab2:** Assessment of Outcome Variables and Confounders for Primary Analysis

Variable type	Variable	Assessment	Time point	Data source	Method of Assessment
**Outcomes**	• Hospital days • Rehospitalisations	Baseline	Point of referral	Secondary data from paper-based records	Data extracted from patient file and entered into referral form by ward staff, then checked by M&E Officer
		Follow-up	Six months from referral	Secondary data from paper-based records	Data extracted from patient file and entered into six-month admissions form by M&E Officer
**Confounders**	• Disability • Family support	Baseline	Initial ward visit after referral	Primary data collected via questionnaire (based on WHODAS 2.0 and MIND ME)	Reported by user to M&E Buddy using baseline form

There are two primary outcomes for this study, both related to change in frequent users’ utilisation of inpatient care at Butabika. The first is change in the number of hospital days over the previous six months. The second is change in the number of rehospitalisations over the previous six months. The index hospitalisation during which the participant was recruited into the study is excluded from both calculations. The study flow chart in Fig. 2 further illustrates the sequence of assessments in each group.

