#### Hospital days

Hospital days are the number of days spent in psychiatric inpatient care at Butabika over the previous six months. In order to calculate the number of hospital days, dates of entry and departure are extracted from the patient file at the point of referral and six months from referral. An entry may be the result of formal admission or return to the hospital’s premises following an escape. Similarly, a departure may be the result of formal discharge or escape from the hospital’s premises.

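### The per-protocol ward-visit rule is not tied to the index stay, so a PSW+ user missed before index discharge can qualify only by being readmitted

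*Protocol article*

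**What the plan says.** The Primary subsection of Analysis plans intention-to-treat and per-protocol difference-in-differences analyses for both primary outcomes. For the per-protocol set, "participants in the PSW+ arm must receive at least one recorded ward visit and three recorded community visits during the six-month follow-up period". No visit rule applies to the PSW- group.

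Elsewhere the article describes the intervention in a fixed order. The abstract expects "at least one inpatient visit by a trained peer support worker before hospital discharge and three to six additional visits after discharge". The Peer support section gives the same order, with the later visits following discharge: "A recipient of peer support will be visited by a PSW at least once on the ward before discharge, and at least three times after". Those later visits take place "either at home, at a meeting point in the community, or at the hospital when the recipient returns for outpatient visits".

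Three further statements decide what the rule does in practice:
- Admissions data are "extracted from hospital records at point of referral and six months following referral", so follow-up begins while the participant is still on the ward.
- "The index hospitalisation during which the participant was recruited into the study is excluded from both calculations" (Outcomes).
- "An entry may be the result of formal admission or return to the hospital’s premises following an escape" (Hospital days), and the number of stays is derived from the same entry and departure data.

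**The concern.** The per-protocol rule replaces the order of ward visit, discharge and later visits with a six-month window. That window covers the index stay and every later stay. Because the index stay is not counted, any later stay on a ward is a rehospitalisation. For users missed at the index stay, the ward-visit requirement can thus be met only by having an outcome event.

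This is selection on the outcome in one group only. The per-protocol contrast is where readers will look for the effect of peer support as delivered. Under this wording the set can include users who did not receive the sequence that the article itself describes, and they enter because they were readmitted. Two analysts could also build different sets, one from the Primary subsection and one from the Peer support section.

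**Working it through.** **1. The plan's own figure.** The pool for the per-protocol set is the 126 PSW+ completers in Study size: 180 × (1 − 0.15 − 0.15) = 126. This reproduces with additive losses; sequential losses would give 180 × 0.85 × 0.85 = 130. The point does not depend on it.

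**2. The rule applied to three PSW+ records**, each with three community visits:

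| Record | Ward visit in index stay | Readmitted | Ward visit in later stay | Literal rule | Index-tied rule |
|---|---|---|---|---|---|
| A | yes | no | – | in | in |
| B | no | no | – | out | out |
| C | no | yes | yes | in | out |

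B and C had the same incomplete start. Only a readmission separates them. The literal set is the index-tied set plus records like C, all of whom have at least one readmission, so it cannot have a lower readmitted share. Visits at the hospital after discharge offer no clear other route, since the article attaches them to outpatient attendance.

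**3. Readmitted share.** The article gives none of the following, so they are assumptions:
- r = share of PSW+ users readmitted
- m = share with no ward visit in the index stay (taken as unrelated to readmission)
- v = chance of a ward visit if readmitted
- k = chance of three community visits if readmitted, relative to not readmitted

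Literal rule: rk(1 − m + mv) / [rk(1 − m + mv) + (1 − m)(1 − r)]. Index-tied rule: rk / [rk + (1 − r)].

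Example with r = 0.30, m = 0.10, v = 1, k = 1: literal 0.30 / (0.30 + 0.63) = 32.3%; index-tied 0.30 / 1.00 = 30.0%.

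With r = 0.30 and v = 1:

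| m | Index-tied, k = 1 | Literal, k = 1 | Index-tied, k = 0.7 | Literal, k = 0.7 |
|---|---|---|---|---|
| 0.05 | 30.0% | 31.1% | 23.1% | 24.0% |
| 0.10 | 30.0% | 32.3% | 23.1% | 25.0% |
| 0.20 | 30.0% | 34.9% | 23.1% | 27.3% |
| 0.40 | 30.0% | 41.7% | 23.1% | 33.3% |

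Over r 0.2 to 0.4, m 0.05 to 0.40, v 0.5 to 1 and k 0.5 to 1, the literal rule adds about 0.3 to 13 percentage points to the index-tied share. With m at 0.05 or 0.10 it adds about 0.3 to 2.6 points.

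**4. Against all PSW+ users.** The literal share exceeds r only if k > (1 − m)/(1 − m + mv). With v = 1 that is k > 0.90 at m = 0.10 and k > 0.80 at m = 0.20. At r = 0.30, m = 0.10, v = 1, k = 0.7 the share is 25.0%, below the 30% in all PSW+ users.

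**5. Number of users and mean count.** Assume gamma-Poisson readmissions with mean 0.8 and shape 1, a ward-visit chance v of 0.4 to 0.7 per readmission, and a 0.6 chance of meeting the community clause whatever the outcome. The chance of at least one visited readmission is 1 − 1/(1 + 0.8v) = 0.24 to 0.36. Users entering only through a later stay number:
- 10% missed: 126 × 0.10 × (0.24 to 0.36) × 0.6 = about 2 to 3
- 30% missed: 126 × 0.30 × (0.24 to 0.36) × 0.6 = about 5 to 8

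On the same inputs the mean follow-up count in the per-protocol set moves from 0.80 to 0.84 at 10% missed, and to 0.93 (v = 0.4) or 0.95 (v = 0.7) at 30% missed. These means hold the community clause independent of the outcome, so they isolate the ward-visit clause and do not describe the whole rule. In a change-from-baseline contrast, part of the excess would cancel if these users also had more stays at baseline.

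**The case against.** The best defence is that the Primary subsection is shorthand. The Peer support section already fixes one visit before discharge and three after, and the rule can be read as naming those same visits. A detailed analysis plan exists and may date them. This explains how the wording could have arisen, but the article does more than stay silent: it states its own window, and that window differs from its definition of the intervention. The sections need reconciling.

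The objections to size stand. No missed-visit or readmission rate is given, and the Peer support section expects every recipient to be seen before discharge, so the missed share may be low. Record C also needs four things within six months of referral: a missed visit, a readmission, a ward visit during it, and three community visits.

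A reader might infer that the rule loads the per-protocol set with readmissions, or biases the whole per-protocol analysis against peer support. The documents support neither. Readmitted users have less time in the community to collect three visits, and step 4 shows that this can outweigh the ward-visit clause. A reader might also set the inflated means beside the 20% effect in Study size. That comparison is unsafe, because the scale of that 20% is worked out in an additional file that is not shown and may not be a relative change in the mean.

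**Conclusion.** The point holds in a limited form. The per-protocol rule accepts a ward visit from a later stay, departs from the article's own description of the intervention, and makes entry depend on the outcome for users missed at the index stay. That follows from the wording alone.

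Relative to an index-tied rule, the direction is fixed: more readmissions in the PSW+ per-protocol set, with no matching selection in PSW-. The amount is unknown, small if few users are missed, and nil if none are. Every figure in steps 3 to 5 rests on assumed rates. The net direction relative to all PSW+ users is not determined. Intention-to-treat is untouched, so what is at stake is the interpretation of the per-protocol result beside it.

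**What to change.** Reconcile the Primary subsection with the abstract and the Peer support section on when the qualifying ward visit must occur. For per-protocol inclusion, require at least one ward visit on record with a date from referral up to the participant's first departure, by discharge or escape, from the index hospitalisation. State that ward visits in a later stay do not count for inclusion. The reference to escape is needed because a return after escape is a new entry; a rule that mentions only discharge would leave part of the same route open. Report how many PSW+ users would have qualified only through a ward visit in a later stay, which shows the size of the problem directly. This concerns the analysis set only, not how visits are delivered.

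The cost is one sentence and a date comparison. Visits are documented on a form completed each time (Table 1, Quality Assurance), and applying the existing six-month window already requires their timing. Entry and departure dates are already extracted (Hospital days). The analysis plan is to be finalised before any data are analysed, so the change can be pre-specified. The downside is a slightly smaller per-protocol set. The change does not remove selection through the community-visit requirement, which still applies to PSW+ only.

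### The per-protocol DID listed under Primary selects PSW+ users on visits that readmission makes less likely, with no matching selection in PSW-, so it should not carry primary status

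*Protocol article*

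**What the plan says.** The subsection Primary under Analysis states: "We will carry out both intention-to-treat and per-protocol DID analyses for the two primary outcomes, presenting adjusted and unadjusted results". It gives neither analysis priority. The per-protocol rule is that "participants in the PSW+ arm must receive at least one recorded ward visit and three recorded community visits during the six-month follow-up period". No inclusion rule is given for the comparison group, which the abstract describes thus: "Frequent users from other districts enter the PSW- group and receive standard care". The effect estimate is the group-by-time term: "The interaction estimating the change from baseline to follow-up in the PSW+ group relative to change in the PSW- group".

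The section Peer support fixes when and where the qualifying visits take place. A recipient is visited "at least once on the ward before discharge, and at least three times after discharge". The later visits happen "either at home, at a meeting point in the community, or at the hospital when the recipient returns for outpatient visits"; a readmission ward is not among the places listed. On duration: "Peer support visits are offered for up to six months after a PSW is assigned to a user".

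The section Outcomes counts hospital days and inpatient stays over six-month windows, with follow-up read from the files six months after referral. The index stay is left out of both counts. The adjusted model adds baseline disability and family support only. Neither the section Bias nor the limitations in the Discussion mention selection through the visit rule.

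**The concern.** To qualify, a PSW+ user must spend enough of the follow-up period out of hospital to be visited three times. Time in hospital over nearly the same period is one primary outcome, and the number of returns to hospital is the other. A user readmitted early, often or for long has less opportunity to qualify and is more likely to be dropped. A PSW- user with the same course stays in.

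DID removes stable differences between the groups. It does not remove a difference created by choosing one group on what happens during follow-up, and covariates measured at baseline cannot undo that choice. If the ITT result were null and the per-protocol result favourable, nothing in this section would stop the second from being presented as a primary finding.

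**Working it through.** **1. The plan's own figure.** The section Study size expects at most 126 PSW+ completers: 180 × (1 − 0.15 − 0.15) = 126, which reproduces. (Sequential losses would give 180 × 0.85 × 0.85 = 130.) With 87 PSW- completers, these are the sizes used below. The PSW+ number is cut to 126 × the share who qualify.

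**2. What the rule estimates when peer support does nothing.** Let Y0 and Y1 be a user's baseline and follow-up counts and V = 1 if the user qualifies. If both groups follow the same event process, then

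- ITT DID = E[Y1 − Y0] − E[Y1 − Y0] = 0
- per-protocol DID = E[Y1 − Y0 | V = 1] − E[Y1 − Y0]

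The second is zero only if qualifying is unrelated to the change. Here V depends on days out of hospital, which is the complement of hospital days.

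**3. Simulation under no effect.** Assumed, not in the article: 0.8 to 1.2 stays per six months; readmission stays of 21 to 45 days; one visit per 20 to 60 days out of hospital; mean remaining index stay of 1 to 60 days. There were 100 settings of 20,000 users each, tested two-sided at 0.05. Percentages are of the baseline mean.

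| Setting | Qualify | DID, stays | DID, days | False-positive rate, stays / days |
|---|---|---|---|---|
| (a) Random visits every 45 d, continuing after readmission; index 21 d, readmission stay 30 d | 62% (126 × 0.62 = 78) | −0.04 | −3.1 | 6% / 8% |
| (b) Scheduled every 45 d, clock restarts at each discharge; same stays | 60% (76) | −0.26 (32%) | −8.5 (35%) | 33% / 27% |
| (c) Scheduled every 45 d, stopping at first readmission; index 1 d | 59% (74) | −0.37 (46%) | −10.4 (45%) | 61% / 39% |
| (d) Random every 30 d, continuing; 1.2 stays; index 60 d | 64% (81) | +0.07 (6%) | −0.8 (2%) | 6% / 5% |

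Over all 100 settings:

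- The days DID was below zero every time, from −0.2 to −11.6.
- The stays DID was zero or below in 90, down to −0.41. It was positive in 10 (at most +0.07), all with a remaining index stay of 45 to 60 days.
- False-positive rates ran from 5% to 61% for stays and from 5% to 39% for days.
- With visits every 20 days the bias was near zero.

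**4. Where the bias comes from.** In (b), 45% of all users but 20% of qualifiers are readmitted. Among the excluded 40% the rate is (0.45 − 0.60 × 0.20) / 0.40 = 0.825. In (c), mean follow-up stays are 0.69 overall and 0.14 among qualifiers, a gap of 0.55. The DID of −0.37 means that subtracting baseline removed only about 0.55 − 0.37 = 0.18 of it.

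**5. A second visit model.** Assumed: each due visit is made with probability 0.8, 0.75 readmissions per 182 days at risk, mean stay 35 days. Results are ratios of qualifiers to the unselected group, 1 being no bias, so they are not on the scale of the percentages above.

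| Visit interval | Remaining index stay | Stays | Days |
|---|---|---|---|
| 14 d | 21 d | 0.98 | 0.91 |
| 21 d | 60 d | 1.04 | 0.85 |
| 30 d | 21 d | 0.86 | 0.61 |
| 30 d | 60 d | 0.97 | 0.68 |
| 45 d | 21 d | 0.66 | 0.32 |

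A further run of 12 settings that compared follow-up means only gave about 0.97 to 0.32 for days and 1.05 to 0.57 for stays.

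**The case against.** The strongest reply is that the bias may be small. Three visits in up to six months is a modest demand. A user can reach it before or after a short readmission, and the section Peer support adds: "For particularly vulnerable cases (i.e. three or more inpatient stays in the past 12 months), up to six visits can be made". Much of this stands: with frequent visits, or with visits that simply resume after readmission as in setting (a), the distortion is modest. A reader might infer that readmission rules a user out; the text does not say so. The extra visits for heavier users are no safeguard, though. In the run that tied visits to prior use, otherwise like (a), the DID grew to −0.16 stays and −6.3 days.

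A reader might also infer that both outcomes must be biased towards the programme, including through users who are never discharged. The documents do not support that. The index stay is excluded from both counts, so such users score zero at follow-up and dropping them works against the programme. This is why the stays bias can vanish or reverse.

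The plan's stated focus is access to a peer support worker, its key contrast is the access-by-time interaction, and ITT is named first and always reported alongside. That is fair: equal standing is read from the absence of a ranking and is not declared. One could go on to count two outcomes, two analysis sets and two adjustments as eight uncontrolled tests. That does not follow, since the adjusted and unadjusted results are versions of one contrast. Error control across outcomes is also a separate matter that the unseen analysis plan may settle.

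**Conclusion.** The concern holds in a limited form. The visit rule selects PSW+ partly on its own follow-up outcome and leaves PSW- unselected, and nothing in the described model repairs that. This follows from the text alone.

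The size does not follow from the text. It rests on assumed visit pace, readmission rate, stay length and what happens to visits after readmission. For hospital days the expected direction is towards the programme in every setting tried. The bias is small at two- to three-week intervals (near zero in the first model, ratios of 0.91 and 0.85 in the second). It reaches 35% to 45% of the baseline mean in the 45-day settings (b) and (c). That exceeds the 20% and 30% effects in Study size, if those are read as proportional reductions, which the article does not define. For rehospitalisations the bias usually points the same way but can be nil or slightly reversed.

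A reader might conclude that the per-protocol analysis will show a benefit where there is none. The documents support only an expected direction, with false-positive rates from no inflation upwards. Because ITT is also planned, the study is not invalidated; the per-protocol result simply should not carry a primary claim.

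**What to change.** In the Primary subsection and in the analysis plan, which is still to be finalised before any data are analysed:

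- Name the ITT DID, the access-by-time interaction, as the only primary analysis for both outcomes.
- Label the per-protocol DID secondary or supportive, state that it selects PSW+ on visits made during the outcome window, and do not use it to claim effectiveness.
- Report visits received descriptively.
- If a dose-related estimate is wanted, use a method that does not select one group on follow-up visits. One option is a landmark applied to both groups, for which entry and departure dates are already extracted. Another is a complier-type estimate with its assumptions written out.

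The cost is wording; no new data are needed. The per-protocol result can no longer support a primary claim. A landmark shortens the period over which outcomes are counted. A complier-type estimate has a wider interval, needs parallel trends between districts that were not randomised, and assumes that fewer than the specified visits have no effect. That last assumption is debatable, so it should be an option and not a requirement.

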**Fig. 3 Fig3:**
[figure not shown]
Initial working model

However, DID is designed to adjust for time-invariant and group-invariant confounders [51]. Age, gender, diagnosis, education level, employment and marital status are unlikely to change substantially between groups within the six-month follow-up period. We also observe cautions by Glymour et al. (2005) regarding adjustment for baseline measures of outcome variables (hospital days and rehospitalisations) [52]. Therefore, we plan to include only the remaining two proposed confounders (disability and family support) as pre-specified covariates in the adjusted analysis.

The M&E Buddy collects data on these two potential confounders by administering a baseline form to the study participant while he or she is still on the hospital wards [Table 2]. For those in PSW+ group, it is completed before any PSW visits take place.

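### Baseline disability and family support, entered as plain covariates, leave the group-by-time estimate essentially unchanged, so the adjusted analysis does not control confounding of change

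*Protocol article*

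**What the plan says.** The Primary analysis section specifies mixed models with "a random effect to account for correlations among users with the same PSW" and with "fixed effects for access to peer support (PSW+ group versus PSW-group), time (baseline versus follow-up"), plus the interaction of the two. It then singles out one coefficient as the target: "The interaction estimating the change from baseline to follow-up in the PSW+ group relative to change in the PSW- group is the key effect of" ... On the form of the model: "We will use multivariable linear regression unless the distribution is skewed, in which case we may consider a Poisson or negative binomial regression". Adjusted and unadjusted results are promised for two outcomes, each by intention to treat and per protocol. The adjustment is described in one clause: "disability and family support are potential confounders and will be included as covariates in the adjusted analysis". No covariate-by-time term is mentioned.

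Under Potential confounders, the M&E Buddy "collects data on these two potential confounders by administering a baseline form to the study participant", and Table 2 lists baseline as the only assessment of the two confounders. The Exploratory section adds that primary data cannot be collected from the PSW- group at six months. The two variables therefore cannot enter as time-varying covariates in both groups.

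Potential confounders also explains why the other candidates are left out: "Age, gender, diagnosis, education level, employment and marital status are unlikely to change substantially between groups within the six-month follow-up period". It concludes: "we plan to include only the remaining two proposed confounders (disability and family support) as pre-specified covariates in the adjusted analysis".

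**The concern.** A difference-in-differences (DID) estimate compares changes. A baseline characteristic biases it when the characteristic predicts change and differs between the groups. Entering that characteristic as a main effect models its relation to the level of the outcome, which the before-after comparison has already removed. Its relation to change is not modelled.

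The reason given for dropping age, gender, diagnosis and the rest has the same gap. A stable characteristic has its constant effect on outcome level differenced out, but it can still confound if, for example, participants with one diagnosis would have improved more over six months anyway and that diagnosis is commoner in one set of districts.

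The groups are defined by district, and the Discussion accepts that factors varying by time and group may confound the comparison. The adjusted analysis is the only statistical control for measured confounders that the article describes. If it returns the unadjusted figure by construction, a reader may take the match as a sign that disability and family support do not matter.

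**Working it through.** **Inputs.** Group, time and their interaction as fixed effects, the interaction as target, a PSW random effect, and a linear model with Poisson or negative binomial as alternatives (Primary). Covariates at baseline only (Table 2, Potential confounders, Exploratory). Completers: 126 PSW+ and 87 PSW- (Study size). The 126 reproduces as 180 × (1 - 0.15 - 0.15) = 126; it serves only as a simulation size. The protocol gives no figure for the adjusted estimate, so there is none to reproduce.

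**Linear model.** For participant i at time t, with group G, time T, baseline covariates X and PSW effect u:

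E[Y_it] = α + βG_i + γT_t + δG_iT_t + θX_i + u

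Subtracting baseline from follow-up gives E[Y_i1 - Y_i0] = γ + δG_i; both θX and u cancel. With complete pairs, the covariate mean in each group is the same at both times, so for any θ

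δ̂ = (mean change in PSW+) - (mean change in PSW-),

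which is the unadjusted estimate.

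**Poisson model, log link.** The score equations make the fitted total in each group-by-time cell equal the observed total Y_gt. The factor in X is the same at both times within a group, so

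δ̂ = log[(Y_11 × Y_00) / (Y_10 × Y_01)],

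with or without X. A PSW random intercept does not alter this: given a participant's two-period total, the follow-up count is binomial with a probability that depends only on group.

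**If X drives change.** Let the true change be γ + δG + λX. Both the unadjusted and the main-effect estimates then centre on δ + λ × (difference in mean X between groups). Adding X × T puts λ in the model and removes that term.

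**Numerical check.** Simulated with 126 and 87 participants, true effect 0, and both covariates imbalanced and driving change (assumed values). One data set, complete pairs:

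| Model | Unadjusted | Covariates as main effects | Covariates × time |
|---|---|---|---|
| Ordinary least squares | -3.632861 | -3.632861 | -0.417549 |
| Linear mixed, PSW intercept | -3.632861 | -3.632861 | -0.417549 |
| Linear mixed, person intercept | -3.632861 | -3.632861 | -0.417549 |
| Poisson (log scale) | -0.132394 | -0.132394 | 0.100569 |
| Negative binomial (log scale) | -0.132394 | -0.122141 | 0.098433 |

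Regressing each participant's change on group plus the two covariates also gives -0.417549, as expected in the linear case. The least-squares standard error fell from 2.016 to 1.452 with main effects, although the estimate was the same number.

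Over 300 data sets with built-in confounding of -3.9, the linear means were -3.87, -3.87 and 0.01; the largest adjusted-unadjusted difference was 4e-14. Negative binomial means were -0.266, -0.260 and 0.027. Over 60 negative binomial runs, the adjusted-unadjusted shift averaged 0.017 in absolute value, with a maximum of 0.053.

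**Missing follow-up records (least squares, same data set).** At 5% missing: -4.17 unadjusted, -3.92 with main effects, -0.81 with covariates × time. At 15% missing: -3.76, -3.71 and -0.70. Some mixed-model and negative binomial fits gave convergence warnings; the exact results above rest on the algebra.

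**The case against.** The strongest reply is that the article does not say the covariates enter as main effects only. The listed fixed effects could be the unadjusted core. The outcomes are defined as changes, and the section opens by comparing six-month change with multivariable linear regression. A change-score regression on group plus covariates fits those words and does adjust. The statistical analysis plan, which is not shown, may settle the form. This reading is possible, but it sits badly with the explicit group, time and interaction structure and with the naming of the interaction as the target. The point stands for the model as written.

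Some stronger readings are tempting, and the documents do not support them:

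- A reader might infer that the adjusted and unadjusted figures must always agree. Exact equality needs complete pairs and a linear or Poisson model. The protocol also allows negative binomial or another method, and Study size allows for 15% loss to follow-up.
- A reader might infer that the protocol's own rule would exclude the two covariates it keeps. Disability and family support can change within six months, and the Exploratory section measures both twice in PSW+. What remains is that the model can use only their baseline values.
- A reader might infer that the authors intend to offer agreement as reassurance. Nothing says so; the Discussion concedes residual confounding and asks for caution.

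The remedy also has limits. In a separate simulated Poisson example with no true effect, an assumed imbalance of 0.5 SD gave a log ratio of 0.4246, and covariate × time still left 0.229 (0.229 / 0.4246 = 54%). In count models the correction works only as far as the assumed form of the covariate's effect on change is right.

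**Conclusion.** The concern holds for the analysis as described. With both records for each participant, the planned adjustment returns the unadjusted interaction exactly in linear and Poisson models; under negative binomial regression or with modest missing follow-up, most of the confounding stays. This applies to four adjusted estimates (two outcomes, each by intention to treat and per protocol). The covariates may change the reported standard error, but they do not control differences in change related to disability or family support.

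The equality rests on the model structure and on baseline-only covariates, and does not depend on the simulated values. The size of any bias in this study is unknown: it depends on the group imbalance and on how strongly each variable predicts change, and the protocol gives neither. The figure of about -3.9 is illustrative. The unadjusted DID, the design and the data collection are unaffected.

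**What to change.** In the adjusted model, include disability × time and family support × time alongside their main effects. In the linear case this is equivalent to regressing each participant's change on group plus the two baseline covariates; that equivalence does not carry over to Poisson or negative binomial models, where the interaction terms should be written out.

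In Potential confounders, replace the stability argument: DID removes a stable characteristic's constant effect on outcome level, but not confounding when the characteristic predicts change and differs by group.

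Interacting other Table 3 variables with time, such as age, gender and diagnosis, is optional and belongs in a sensitivity analysis, given about 126 + 87 = 213 completers and the parameters that a multi-category diagnosis would use.

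The cost is a change of wording in the protocol and analysis plan and, for the required part, a few degrees of freedom. All the variables are already collected.
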